#### Statistical analyses.

Statistical analyses of SCED data have gained prominence in recent years and will be used as a complementary method of data evaluation. There are still, however, no agreed-upon criteria for statistical analysis of SCED data [60]. Data from the frequently administered measures will be displayed and analyzed using the Shiny app for Single-Case Data Analysis [57]. The generated graphs will support visual analysis, and regression analysis will be conducted for quantitative assessment. Randomization tests (RTcombiP; [61]) will be applied to evaluate if levels of social cognition problems, social communication, social interaction, social problems, and neuropsychiatric problems differ significantly between phases (baseline versus treatment + follow-up).

If visually analysis yields strong or moderate evidence, effect size estimates will be calculated using non-overlap of all pairs (NAP) for the dependent variables: social cognition problems, social interaction, social communication, neuropsychiatric problems, and neuropsychiatric problems. To assess individual improvements on the periodic measurements (BAFQ, DEX, IRI, FEEST, Cartoon test, LCQ, DMSCQ, NPI-Q), the Reliable Change Index (RCI) will be calculated. The RCI will indicate whether post-treatment and follow-up changes are both statistically and clinically significant.

Reporting of the study will follow the Single-Case Reporting guideline In Behavioral interventions (SCRIBE) checklist [53], consisting of 26 items that outline the structure of a SCED report.

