#### Randomization.

The multiple baseline design will be used to strengthen internal validity by controlling for threats such as history and maturation (i.e., in the case of brain injury spontaneous or natural recovery should be considered). Three different baseline lengths will be used: start treatment within 16–20 days, 21–27 days, or 28–33 days. This setup ensures that no participant waits longer than 4 weeks before starting T-ScEmo treatment, which aligns with the average waiting period for non-participating patients. The participants are randomly assigned to a baseline length by using a randomization tool. Randomization applies only to baseline length; all participants receive the intervention.

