### Sample size

We aim to include at least 8 patients and their significant others (i.e., 16 participants in total), with a maximum of 20 patients and their significant others (i.e., up to 40 participants). According to Tate et al. (2019) [56], a minimum of 3 participants is generally recommended to ensure sufficient variability and reliability of the data, as well as meet evidence standards. Moreover, replication across at least 3 participants is essential to draw robust conclusions. Given that the study design consists of 3 different baseline lengths – each considered a separate experiment in terms of the SCED design standards – it is ideal to include at least 3 participants per 3 baseline condition (i.e., a total of 9 participants) [56].

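### With three randomized baseline lengths a single-patient p-value cannot fall below 1/3, so at the minimum of 8 patients the usual p-value combinations cannot reach 0.05

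*Protocol article*

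**What the plan says.** The Randomization section of the protocol article sets the allocation: "Three different baseline lengths will be used: start treatment within 16–20 days, 21–27 days, or 28–33 days". It adds: "The participants are randomly assigned to a baseline length by using a randomization tool". It limits the random element further: "Randomization applies only to baseline length; all participants receive the intervention". No random draw of the day inside a window is described.

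The Sample size section gives the range: "We aim to include at least 8 patients and their significant others (i.e., 16 participants in total), with a maximum of 20 patients". It names 9 (three patients at each of three lengths) as ideal. These numbers rest on a replication rule of thumb, not on what the test can detect.

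The Statistical analyses section says: "Randomization tests (RTcombiP; [61]) will be applied to evaluate if levels of social cognition problems", with further outcomes listed, "differ significantly between phases (baseline versus treatment + follow-up". It gives no alpha, no rule for combining p-values and no set of admissible assignments. It places statistics alongside visual analysis as a supplement, plans regression on the same ratings, and makes the non-overlap effect size conditional on the visual result.

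**The concern.** A randomization test gets its validity from the assignments that could actually have occurred. With three possible assignments per patient there are only three possible ranks, so the p-value of one patient is very coarse. Combining 8 coarse p-values with formulas built for continuous ones can leave the smallest possible result above the usual threshold.

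The issue arises from three choices that the protocol does state: the allocation, the test and the minimum sample. If the study closes at or near its minimum, a strong and consistent effect could be reported as non-significant because of the test, and readers could take that as evidence against the treatment. The study would also lose the one analysis that uses the randomization on which the Discussion relies for internal validity.

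**Working it through.** The protocol reports no power or alpha calculation to reproduce. Its sample-size arithmetic is correct: 3 × 3 = 9, 8 × 2 = 16, 20 × 2 = 40.

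**Inputs.** Three lengths, each assumed to have probability 1/3 (Randomization). N from 8 to 20, ideal 9 (Sample size). Assumed because not stated: alpha 0.05; RTcombiP combines single-patient p-values.

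**Single-patient floor.** 1 / (number of possible assignments) = 1/3. The possible values are 1/3, 2/3 and 1.

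**Combined floor when every patient is at 1/3.**

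- Additive (Edgington): p = Σ(−1)^k C(N,k)(S−k)^N / N!, summed over k ≤ S, where S is the sum of the p-values.
  - N = 8, S = 8/3: (2557.11 − 476.30 + 1.09) / 40320 = 0.0516.
  - N = 9, S = 3: (19683 − 4608 + 36) / 362880 = 0.0416.
  - N = 9 with one patient at 2/3, S = 10/3: (50805.26 − 18451.58 + 479.46 − 0.00) / 362880 = 0.0905.
- Fisher: −2N ln(1/3) on 2N degrees of freedom. N = 8: 17.58 on 16, p = 0.349.
- Stouffer: 1 − Φ(√N × z(2/3)). N = 8: √8 × 0.431 = 1.218, p = 0.112.
- Joint test over all assignments: (1/3)^N. N = 8: 1/6561 = 0.00015. If group sizes were fixed at 3/3/2 there would be 560 arrangements and a floor of 0.0018.

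| N | Additive | Stouffer | Fisher | Joint |
|---|---|---|---|---|
| 8 | 0.0516 | 0.112 | 0.349 | 0.00015 |
| 9 | 0.0416 | 0.098 | 0.346 | 0.00005 |
| 12 | 0.0223 | 0.068 | 0.335 | 0.0000019 |
| 20 | 0.0046 | 0.027 | 0.308 | below 10^-9 |

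The first N that can reach 0.05 is 9 (additive), 15 (Stouffer) and 290 (Fisher).

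**Slack above the additive floor.** At N = 9 or 10 every patient must rank first. At N = 12 one patient may rank second (p = 0.048). At N = 20 the p-values may exceed the floor by three steps of 1/3 in total (p = 0.035).

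**Power by simulation.** Assumptions: starts at day 18, 24 or 30; daily then twice-weekly ratings; AR(1) correlation 0.3. Ranges span separate runs.

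| Effect | N | Additive | Joint |
|---|---|---|---|
| Immediate 1 SD | 8 | 0% | 58–69% |
| Immediate 1 SD | 9 | 1–2% | 59–73% |
| Immediate 1 SD | 12 | 4% | 82–87% |
| Immediate 1 SD | 20 | 0–4% | 88–97% |
| Gradual 1 SD | 8 | 0% | 9–10% |
| Gradual 1 SD | 20 | not run | 13–19% |

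The gradual effect builds over the treatment phase (in one set of runs, linearly over 22 weeks). The 0% entries at N = 8 follow from the floor. Type I error of the joint test was 3–5%.

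The low additive power has a simple source. With a true immediate 1 SD shift, a patient ranks first only about 66% of the time. At N = 9 all nine must do so: 0.66^9 = 0.024. At N = 20 about 20 × 0.34 = 6.8 patients are expected to miss first rank, against an allowance of three steps.

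**The case against.** A reader might infer that 8 patients can never give a significant result, however strong the effect. The documents do not support that. Alpha, the combination rule and the workings of RTcombiP are not stated, and a fuller plan may hold them. Pearson's rule would reach 0.018 at N = 8, and a joint test 0.00015. The limit belongs to the additive, Stouffer and Fisher rules at alpha 0.05. This part of the objection stands, so the finding is conditional.

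The floor of 1/3 also depends on how the day is set. The windows cover 5 + 7 + 6 = 18 days. If the day itself were randomized, the floor would fall to about 1/18 and the problem at N = 8 would vanish. The text, however, describes randomization to a length only, and days that were not randomized cannot validly enter the reference set.

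Under the additive rule the miss at N = 8 is only 0.0516 − 0.05 = 0.0016, and the ideal of 9 clears it. That is true of the floor, but one more patient is no remedy: power at N = 9 is 1–2% for an immediate 1 SD shift, and 21% even for 2 SD.

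A second tempting inference is that the primary question cannot be answered positively. That also fails. Visual analysis comes first and has its own grading of evidence, and regression is planned as well.

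Finally, the advantage of a joint test should not be oversold. Treatment runs 20 to 25 weeks and the behaviour-regulation module starts at session 12, so a full shift on the start day is the favourable case. For a gradual 1 SD effect, joint power is only about 10% at N = 8. This stands and must accompany the recommendation.

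**Conclusion.** The concern holds in conditional form. Given equal allocation among three lengths and no random draw of the day, no single patient can show a significant phase difference. If single-patient p-values are combined by the additive, Stouffer or Fisher rule at alpha 0.05, the planned test cannot be significant at the stated minimum of 8. Above 8, additive power for an immediate 1 SD shift stays near zero to 4% up to the maximum of 20, and Fisher remains out of reach throughout. The consequence is loss of randomization-based support for the conclusion, not a predetermined answer to the primary question.

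**What to change.** Replace the combination of p-values with one joint randomization test per outcome. The statistic is the mean over patients of (post-start mean minus baseline mean). The reference set is all 3^N assignments of the three lengths, or the restricted set if allocation was restricted. State alpha and the admissible assignments. State that single-patient p-values cannot be below 1/3, and report single-patient results as estimates without significance claims.

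The cost is a few lines of code and a short addition to the analysis section, with no extra patients or ratings. The protocol defers analysis until data collection is complete, expected in April 2027, so the change can be made before results are seen.

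Two downsides should be disclosed. No per-patient significance statement will be made, although none was attainable with three lengths. The joint test has little power against an effect that builds gradually, so the plan should say in advance that a non-significant result is not evidence of no effect.

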**Methods and analysis:**

A non-concurrent, randomized, multiple-baseline single-case experimental design (SCED) will be employed to investigate the effectiveness of T-ScEmo in this study. At least 8 participants and a significant other will be randomly assigned to one of three baseline lengths. The primary outcome measures (social functioning, neuropsychiatric problems, relationship quality) will be assessed daily during baseline and twice a week during the treatment and maintenance phases. Secondary outcomes will be assessed at T0 (pre-treatment), T1 (post-treatment), and T2 (1-year follow-up). Both patients and the significant other will complete all outcome measures.

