Although the effectiveness of T-ScEmo has been demonstrated in individuals with TBI, it remains unknown whether the treatment is also effective in individuals with ABI and comorbid neuropsychiatric problems. Therefore, the primary aim is to examine the effect of T-ScEmo on social functioning in patients with ABI and comorbid neuropsychiatric problems (RQ1). Secondary aims include examining the effects of T-ScEmo on neuropsychiatric problems and quality of partner relationships in this population (RQ2).

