### Primary outcome measure

*Satisfaction with social functioning* is assessed using a Social Functioning Scale (SFS), in which patients and significant others rate the patient’s functioning in social situations on a 10-point Likert scale ranging from 1 (“not at all”) to 10 (“entirely”). The item presented is: “How satisfied are you today with your (or your significant other’s) functioning in social situations?” To ensure a sufficient number of data points, as recommended for SCED studies, the SFS will be completed frequently: daily during phase A (2–4 weeks) and twice per week during phases B (20–25 weeks) and C (13–21 weeks). The SFS will be completed by both the patient and a significant other online (M-Path).

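### The randomization test and NAP lists omit the primary SFS and the RQS, name constructs that mostly match no repeated scale, and use a phase contrast that does not fit the four phases

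*Protocol article*

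**What the plan says.** The Introduction makes social functioning the primary aim (RQ1) and adds: "Secondary aims include examining the effects of T-ScEmo on neuropsychiatric problems and quality of partner relationships in this population (RQ2". Under Primary outcome measure, satisfaction with social functioning "is assessed using a Social Functioning Scale (SFS), in which patients and significant others rate" the patient. Table 1 marks only the SFS as primary. It schedules the SFS, NPS and RQS daily in baseline (A) and twice a week in treatment (B) and maintenance (C), with one more measurement at follow-up (D/T2). The abstract differs: "The primary outcome measures (social functioning, neuropsychiatric problems, relationship quality) will be assessed daily during baseline and twice a week".

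Statistical analyses contains three relevant statements:

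- Plots and regression: "Data from the frequently administered measures will be displayed and analyzed using the Shiny app".
- Randomization tests (RTcombiP) are to "evaluate if levels of social cognition problems, social communication, social interaction, social problems, and neuropsychiatric problems differ significantly between phases (baseline versus treatment + follow-up". NAP, computed if visual evidence is strong or moderate, is for "social cognition problems, social interaction, social communication, neuropsychiatric problems, and neuropsychiatric problems".
- RCI: "To assess individual improvements on the periodic measurements (BAFQ, DEX, IRI, FEEST, Cartoon test, LCQ, DMSCQ, NPI-Q".

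Phases and measurements defines baseline, treatment, maintenance and follow-up as four separate phases.

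**The concern.** The variables named for the randomization test and NAP are not the variables the design was built to test. The SFS answers RQ1 and the RQS is the repeated measure for the relationship part of RQ2, yet neither is in either list. The NAP list gives neuropsychiatric problems twice, which suggests a drafting slip. The phase contrast does not mention maintenance, although phase C has its own twice-weekly series.

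The randomization test is the only planned analysis that uses the one randomized element of the trial, the baseline length. Followed literally, the text leaves the primary outcome out of that test and applies it to some measures on which it cannot work. The abstract adds a conflict over which outcome is primary.

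**Working it through.** The plan states no figure for this point, so the check maps the lists to Table 1 and counts planned observations.

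**Step 1. Each listed construct against Table 1**

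| Construct in the lists | Instrument in Table 1 | Schedule |
|---|---|---|
| Social communication | LCQ | T0, T1, T2 |
| Social cognition problems | mainly BAFQ-SOC, DEX, IRI, FEEST, Cartoon test | T0, T1, T2 |
| Social interaction | none described as such | – |
| Social problems (randomization test only) | none described as such | – |
| Neuropsychiatric problems (twice for NAP) | NPS | daily in A, twice weekly in B and C |

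Of the five tested constructs, one matches a repeated scale, two map to periodic instruments (one clearly, one mainly) and two have no named instrument. Of the three repeated scales, one (NPS) is recognisable and two (SFS, RQS) are absent.

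**Step 2. A start-point randomization test on T0/T1/T2 data**

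The Randomization section gives start windows of 16–20, 21–27 and 28–33 days. T0 precedes, and T1 and T2 follow, every start from day 16 to day 33. The split is always 1 value before and 2 after. With illustrative scores of 10, 14 and 15, the statistic is (14 + 15)/2 − 10 = 4.5 for all 18 start days, so p = 18/18 = 1. NAP would rest on 1 × 2 = 2 pairs. By contrast, an illustrative daily/twice-weekly series gave 5 distinct statistics for the 5 start days of the first window.

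**Step 3. Planned ratings after baseline, per rater and scale**

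- B: 20–25 weeks × 2 = 40–50
- C: 13–21 weeks × 2 = 26–42
- D: 1
- Total: 40 + 26 + 1 = 67 to 50 + 42 + 1 = 93

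**Step 4. Literal reading: treatment plus follow-up means B + D**

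Ratings kept: 41–51. Ratings dropped: 26–42.

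- Smallest share dropped: 26/(50 + 26 + 1) = 26/77 = 34%
- Largest share dropped: 42/(40 + 42 + 1) = 42/83 = 51%

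**Step 5. Loose reading: follow-up includes C, so B and C are pooled**

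Suppose a constant gain throughout B, zero in C, and unweighted means. The fraction of the gain that the pooled contrast shows is B/(B + C).

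- Lowest: 40/(40 + 42) = 40/82 = 49%
- Highest: 50/(50 + 26) = 50/76 = 66%

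Counting the single D rating as zero too gives 40/83 = 48% and 50/77 = 65%.

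**Step 6. Which contrast the randomization supports**

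Only the A/B start point is randomized. Moving it reassigns observations between A and B and leaves the labels of C and T2 unchanged. A versus B is therefore the contrast the randomization supports directly.

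**The case against.** The strongest reply is that these are loose labels. Table 1 puts the SFS under the heading Social cognition, so the authors may have meant the SFS by social cognition problems, and follow-up may mean everything after treatment. The periodic measures are expressly assigned to the RCI, so a randomization test on three time points may never have been intended. This is plausible, but the text does not say it. The SFS item asks about satisfaction with functioning, and the Hypotheses section treats social cognition problems and social communication and interaction as separate expected effects. Maintenance and follow-up are defined as distinct phases. Step 2 therefore shows why the lists cannot stand as worded; it does not predict what the team will do.

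Several stronger inferences are tempting and should not be drawn:

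- *The primary outcome goes unanalysed.* The SFS is a frequently administered measure, so it gets visual analysis and regression. The article presents statistics as complementary to visual analysis, which carries the evidence rule.
- *The relationship hypothesis has no analysis.* The RQS gets the same treatment, and the DMSCQ gets an RCI.
- *Sustained change is ignored.* The RCI covers follow-up, and visual analysis covers duration of change.
- *None of the listed tests can be run.* Neuropsychiatric problems can be tested on the NPS.
- *The unblinded investigator may choose the primary series after seeing the data.* Table 1, the Introduction and the outcome section all make social functioning or the SFS primary. The Blinding section bars analysis until collection is complete and grants no such choice. The lead rater may be fixed in a fuller document.

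**Conclusion.** The point holds as an internal contradiction in the published text, not as a detail left to an analysis plan. The SFS and RQS have no stated place in the randomization test or NAP, and four of the five tested constructs match no repeated scale by name. The contrast either drops 34–51% of planned post-baseline ratings or pools C with B. Pooling would let a gain lost after treatment still show about half to two thirds of its size. The two sets of figures belong to alternative readings and do not add up. They assume complete ratings at the stated phase lengths; the second set also assumes a constant gain in B, none in C, and unweighted means.

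The damage is confined to the randomization test, NAP and the abstract's labelling. It still needs correcting before analysis, because it concerns the primary outcome in the one analysis that uses the randomization.

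**What to change.** 1. Replace both variable lists with SFS (primary) and NPS and RQS (secondary). Keep BAFQ, DEX, IRI, FEEST, Cartoon test, LCQ, DMSCQ and NPI-Q for the RCI only.
2. Make A versus B the randomization-test contrast. Report phase C and T2 separately, by visual analysis, NAP or regression, as evidence of maintenance. A randomization test of A against C plus T2 would be poorly supported, for the reason in Step 6.
3. State before analysis whether the patient's or the significant other's SFS series leads; the other is supportive.
4. Correct the abstract so that only the SFS is primary.

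The cost is wording plus one descriptive contrast per outcome. No new data are needed, since every series is already scheduled. Data collection is expected to finish in April 2027 and the investigator is not to analyse before then, so the change can be made before results are seen.

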## Methods

### Study design

#### Phases and measurements.

A non-concurrent, randomized, multiple-baseline single-case experimental design (SCED) will be used in this study. In a SCED study, participants are repeatedly measured during all phases. The current study will be divided into four phases: baseline, treatment, maintenance, and follow-up. Repeated and frequent measures of the target behavior will be conducted within each phase. The rule of thumb is to collect data at least three, preferably five times per phase [38,39]. The primary outcome measure will be assessed daily during the baseline phase and twice a week in the treatment and maintenance phase. All secondary outcome measures will be assessed at T0 (baseline); a subset will also be assessed at T1 (post-treatment) and T2 (follow-up; 3–5 months post-treatment). See Table 1 and Fig 1 for an overview of the phases and measurements included in this study, including both primary and secondary outcome measurements.

**Table 1 pone.0358008.t001:** Overview of the phases and measures T-ScEmo4ALL Plus^+^.

Tests and questionnaires	Description	T0	Baseline (A)	Treatment (B)	T1	Maintenance (C)	Follow-up (D)/T2
Phase duration (weeks)			2 up to 4	20 up to 25		13 up to 21	

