** *Social cognition* **							
Social Functioning Scale (SFS)	Functioning in social situations	●	● (daily)	● (twice a week)		● (twice a week)	●
Brock’s Adaptive Functioning Questionnaire – social scales (BAFQ-SOC) [41,42]	Social monitoring, empathy	▲			▲		▲
Dysexecutive Questionnaire – social scales (DEX) [43]	Metacognition, social convention, behavioral emotional self-regulation	▲			▲		▲
Interpersonal Reactivity Index (IRI) [44]	Cognitive and affective components of empathy	▲			▲		▲
La Trobe Communication Questionnaire (LCQ) [45]	Communication quality	▲			▲		▲
Cartoon test [46]	Mental state attribution	▲			▲		▲
Facial expression of emotion: stimuli and tests (FEEST) [47]	Facial affect recognition	▲			▲		▲

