** *Partner relationship* **							
Relationship Quality Scale (RQS)	Perceived quality of relationship with significant other	▲	▲ (daily)	▲ (twice a week)		▲ (twice a week)	▲
Dutch Marital Satisfaction and Communication Questionnaire (DMSCQ) [48]	Marital satisfaction, negative communication and open communication	▲			▲		▲

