**SIGNIFICANT OTHERS**							
** *Social cognition* **							
Social Functioning Scale (SFS)	Functioning in social situations	●	● (daily)	● (twice a week)		● (twice a week)	●
Brock’s Adaptive Functioning Questionnaire – social scales (BAFQ-SOC) [41,42]	Social monitoring, empathy	▲			▲		▲
Dysexecutive Questionnaire – social scales DEX [43]	Metacognition, social convention, behavioral emotional self-regulation	▲			▲		▲
La Trobe Communication Questionnaire (LCQ) [45]	Communication quality	▲			▲		▲

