** *Neuropsychiatric symptoms* **							
Neuropsychiatric Problems Scale (NPS)	Severity of neuropsychiatric (behavior) problems, e.g., irritability, aggression, depression, anxiety	▲	▲ (daily)	▲ (twice a week)		▲ (twice a week)	▲
Neuropsychiatric Inventory Questionnaire (NPI-Q) [51]	Neuropsychiatric symptoms	▲			▲		▲

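### The Reliable Change Index is said to show clinical as well as statistical significance, but it can show only that a change exceeds measurement error

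*Protocol article*

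**What the plan says.** The Statistical analyses section of the protocol article assigns the RCI to the measures taken at fixed time points: "periodic measurements (BAFQ, DEX, IRI, FEEST, Cartoon test, LCQ, DMSCQ, NPI-Q), the Reliable Change Index (RCI) will be calculated". It then fixes the interpretation: "The RCI will indicate whether post-treatment and follow-up changes are both statistically and clinically significant".

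The time points come from the section on phases and measurements. All secondary measures are taken at T0, and "a subset will also be assessed at T1 (post-treatment) and T2 (follow-up; 3–5 months post-treatment". Table 1 schedules every instrument on the RCI list at T0, T1 and T2 and marks them all as secondary outcomes.

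The article gives no further criterion for clinical significance, such as a normative cut-off, a return to the normal range or a minimal important difference. It also gives no RCI cut-off and no reliability for any instrument.

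**The concern.** The RCI is a change score divided by the standard error of a difference between two fallible measurements. A large value means that measurement error alone is an unlikely explanation for the change. It does not say whether the change matters to the patient, or whether the patient has moved out of the impaired range. The sentence makes this one statistic the indicator of both.

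This is a statement in the plan, not a gap that a later analysis plan would be expected to fill. A more detailed document could add a clinical criterion, but the published sentence would still be wrong.

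At stake are the individual-level conclusions on the secondary measures. The RCI is the only analysis that the section ties to these instruments by name. One of them, the FEEST, carries a specific hypothesis of improvement in the Hypotheses section. If reliable change is reported as clinically significant change, the article's conclusions on who benefited will claim more than the data can show.

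**Working it through.** The plan gives no figure for this analysis, so there is none to reproduce. Two things can be worked out: what the RCI threshold means in SD units, and how many RCIs the schedule produces.

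**1. What the threshold measures**

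In its usual form, RCI = (follow-up score − T0 score) / (SD × √(2(1 − r))), where r is the reliability. Assuming the conventional cut-off of 1.96, the smallest change that counts, in baseline SD units, is 1.96 × √(2(1 − r)). The reliabilities below are illustrative.

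| r | Calculation | Change needed (SD) |
|---|---|---|
| 0.70 | 1.96 × √0.60 | 1.52 |
| 0.80 | 1.96 × √0.40 | 1.24 |
| 0.90 | 1.96 × √0.20 | 0.88 |
| 0.95 | 1.96 × √0.10 | 0.62 |

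Only r enters the formula. Across this range the required change differs by a factor of 1.52 / 0.62 ≈ 2.5, for a reason unrelated to clinical meaning.

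Errors are possible in both directions:
- A patient who moves from −3.0 to −2.1 SD on a scale with r = 0.90 changes by 0.90 SD. That exceeds 0.88 SD, so the change would be called clinically significant although the patient is still well below the norm. The scores are invented for illustration.
- On a scale with r = 0.70, a change of 1.2 SD that matters to the patient would be refused the label, because it falls short of 1.52 SD.

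**2. How often the label would be applied by chance**

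Count from Table 1, taking one total score per instrument:
- Patient: BAFQ-SOC, DEX, IRI, LCQ, Cartoon test, FEEST, DMSCQ = 7.
- Significant other: BAFQ-SOC, DEX, LCQ, NPI-Q, DMSCQ = 5.
- Change scores per instrument: T0 to T1 and T0 to T2 = 2.
- Total per dyad: (7 + 5) × 2 = 24. Separate analysis of subscales would raise this.

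With no true change and a 1.96 cut-off, each RCI has a 2.5% chance of showing improvement:
- Expected per dyad: 24 × 0.025 = 0.6.
- Over the minimum of 8 dyads (Sample size section): 8 × 0.6 = 4.8.
- Over the maximum of 20 dyads: 20 × 0.6 = 12.
- With a looser cut-off of 1.645: 24 × 0.05 = 1.2 per dyad.

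For a given cut-off, these expected counts do not depend on how the scales are correlated. The probability that a dyad shows at least one chance improvement does:

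| Assumption (1.96 cut-off) | P(at least one) |
|---|---|
| 24 independent comparisons, 1 − 0.975^24 | 0.455 |
| Shared T0 score only (simulated) | 0.425 |
| Shared T0, between-scale error correlation 0.3 | 0.33 |
| Shared T0, correlation 0.5 | 0.26 |
| Shared T0, correlation 0.7 | 0.19 |

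The independence figure is therefore close to an upper bound. Both change scores share the same T0 value, and each rater completes several overlapping social scales.

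**The case against.** The strongest defence is that little depends on this sentence. The Social Functioning Scale is primary and is not analysed by RCI. The daily and twice-weekly neuropsychiatric and relationship scales also address the secondary questions and are not on the RCI list. The section calls statistical analysis complementary to visual analysis. All of this stands. It limits the reach of the error, but it does not make the sentence correct.

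A reader might also infer stronger points, which the document does not support:

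- **That the plan lacks multiplicity control or a key secondary measure.** Such rules are commonly left to an analysis plan or full protocol, neither of which is shown. The count of 24 shows only the scale of the mislabelling.
- **That practice gains on the FEEST and Cartoon test will be counted as treatment effect.** The article does not say which form of the RCI will be used, and a retest correction is normal analysis-plan detail. It gives no figure for retest gains, and T0 and T1 are separated by a treatment phase of 20 to 25 weeks.
- **That every reliable change will be mislabelled.** Some reliable changes will also be clinically meaningful; the RCI cannot tell which.
- **That chance improvements are certain in every dyad.** The 0.6 is an average, and it rests on a cut-off that the article does not state.

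A further fair point concerns the remedy. A rule that every clinically significant change must cross a normative cut-off would not work throughout. Table 2 requires impairment on only some tests or questionnaire scales, and accepts frontal lesions as an alternative indication. Some T0 scores may therefore already be in the normal range, and the article does not show that every instrument has norms.

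**Conclusion.** The statement is wrong as written. The RCI can support a claim of reliable change on each periodic measure, but not one of clinical significance, and no other criterion in the article supplies that. In SD units its threshold is set by reliability: roughly 0.62 to 1.52 SD for reliabilities of 0.95 down to 0.70. The label would thus have no constant clinical meaning across instruments. With no true change, about 0.6 improvements per dyad would be expected to receive it by chance.

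The conclusion that the RCI does not measure clinical importance needs no assumption. The figures rest on a 1.96 cut-off, illustrative reliabilities and one total score per instrument. The consequence is confined to secondary, individual-level conclusions; the primary analysis is untouched.

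**What to change.** Reword the sentence so that the RCI indicates only whether a T1 or T2 change exceeds measurement error, and remove the clinical claim from it. If clinical significance is to be reported, add a second condition: the change must be reliable and must also meet a separate prespecified criterion. Crossing a normative cut-off is one example, used where the instrument has such a cut-off and the T0 score lay in the impaired range. Where these conditions are not met, report reliable change only.

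No new data collection is needed. Table 2 already relies on scores that indicate impairment, so thresholds are evidently in use for at least some measures. The criterion can still be set without knowledge of results. The Procedure section expects data collection to end in April 2027, and the Blinding section keeps the investigator from analysing data before it is complete.

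The cost is a wording change, a decision for each instrument on whether a usable criterion exists, and fewer changes labelled clinically significant.
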